**Methods and analysis:**

A randomised controlled trial involving 75 patients with patellofemoral osteoarthritis from nine different clinical centres in Switzerland, Germany and Croatia is being conducted to evaluate the effectiveness of N-TEC implantation compared with standard treatment with platelet-rich plasma (PRP). In the intervention group, an autologous nasal cartilage cell-derived graft is implanted into the cartilage defects of the patella and/or trochlea during an open surgical procedure. The control group receives three PRP injections at weekly intervals. The primary outcome is the mean Knee Injury and Osteoarthritis Outcome Score Pain Change from baseline to 24 months between groups. Secondary outcomes, including patients’ self-assessed questionnaires, X-ray and MRI scans, physiotherapeutic assessments and safety, will be assessed and compared between the intervention and control group. In addition, the study is complemented with a health-economic evaluation to establish the intervention’s value for money and impact on productivity in working-age individuals. The planned duration of the study is 4 years including baseline and follow-up measurements at 6, 12 and 24 months.

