### Sample size {14}

The sample size was estimated assuming that the data will be analysed in a linear model with treatment as the variable of interest and KOOS at baseline as a covariate. It is assumed that patients will be randomised 1:1 (N-TEC:PRP). Based on published data, we assumed that the SD of the KOOS is 17.2 (pooled SD in both arms at baseline, number of patients: 183).^41^ Furthermore, we assumed that patients treated with PRP gain 10 points, whereas patients with N-TEC improve 25 KOOS pain units from baseline to 24 months. Recruiting a total of 75 patients allows to estimate a difference in the change in KOOS between the intervention arm and the control arm of 15 points with a power of over 90% and a two-sided alpha of 5%, assuming a dropout rate of 20% (15 patients).

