### Plans to promote participant retention and complete follow-up {18b}

Data will be collected until the time of withdrawal using the questionnaires and MRIs at the time of follow-up. No data will be collected afterwards. A final medical visit is recommended for the safety of the patient after withdrawal (minimum 1 year after treatment).

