## Statistical methods

### Statistical methods for primary and secondary outcomes {20a}

The primary analysis will be based on the per-protocol estimand. Follow-up (change from baseline to 24 months) KOOS Pain values will be compared between the treatment arms using a linear regression model including baseline values as covariate (analysis of covariance (ANCOVA)) and centre as fixed effect. The model-based estimate of the treatment effect of tissue implantation as compared with plasma injection together with its 95% CI and p value will be presented. At the moment, the number of patients with a recurrent event is not assessable. Depending on this number and the distribution between the treatment arms, the per-protocol estimand may not be conservative. Therefore, the main estimand will be presented with the intention-to-treat estimand, and the number of intercurrent events will be listed by treatment arm. Possible bias due to intercurrent events will be discussed together with the results.

For demographic baseline variables, summary statistics will be presented. Continuous variables will be summarised by mean and SD in case of an assumed normal distribution or by median and IQR otherwise. Binary and categorical variables will be summarised by frequencies and percentages. KOOS Pain scores at 6 and 12 months as well as further KOOS subscales will be analysed in a similar fashion as the primary outcome namely based on ANCOVA, with the outcome as the dependent variable, the treatment arm as predictor and the baseline outcome value as covariate. The estimated, baseline-adjusted treatment effect of tissue implantation as compared with plasma injection will be reported together with its 95% CI. In case there are centres with fewer than five patients, these will be pooled with the next largest centre. Furthermore, summary statistics will be presented for the values at each assessed timepoint according to treatment arm, with outcomes summarised by mean and SD in case of an assumed normal distribution and by median and IQR otherwise. We will display the time course of the outcomes by appropriate graphics. Treatment failures will be summarised by frequencies and percentages. The proportion of patients with deterioration and non-response will be shown according to Iwano class.

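### Treatment failures get only raw counts and percentages, with no between-arm estimate and no allowance for follow-up that ends at withdrawal

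*Protocol article*

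**What the plan says.** The statistical methods section {20a} deals with this outcome in one sentence: "Treatment failures will be summarised by frequencies and percentages". A further sentence shows deterioration and non-response by Iwano class. In the same section, KOOS Pain at 6 and 12 months and the other KOOS subscales receive a baseline-adjusted treatment effect with a 95% CI. The abstract says that secondary outcomes "will be assessed and compared between the intervention and control group", and the secondary objectives name treatment failures as of interest.

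The outcomes section {12} defines failure by two routes. One is a switch to another regenerative operation or to knee replacement. The other is pathological findings tied to patient complaints, with a KOOS fall of more than 13 from baseline. The first can happen on any day; the second can be seen only when KOOS is recorded, at 6, 12 and 24 months.

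On follow-up, section {18b} states "Data will be collected until the time of withdrawal using the questionnaires and MRIs at the time of follow-up" and then "No data will be collected afterwards". The sample size section {14} reaches its total "assuming a dropout rate of 20% (15 patients" of 75). The missing-data section {20c} is framed around the primary endpoint and names nothing for failures.

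**The concern.** A count and a percentage describe failures fully only if every patient is observed for the same 24 months. By the plan's own figures, about one patient in five will not be. Someone who withdraws at month 7 and has a knee replacement at month 10 is recorded as withdrawn, not as failed. The percentage then depends on where such patients are placed: in the denominator as non-failures, or out of it.

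Two things are at stake. First, the reported figure would be read as a 24-month failure risk, and under either of these placements it is not one. Second, two percentages without a difference or interval are a thin version of the comparison that the abstract promises, with about 37 patients per arm. Unequal loss is also foreseeable. Patients know their treatment, and section {11b} lists contaminated or unsuccessful manufacture as reasons for exclusion, which can arise only in the N-TEC arm.

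**Working it through.** **Inputs from the protocol.** Total 75, allocated 1:1, so 37.5 per arm on average; dropout 20% (15 patients); follow-up 24 months; primary difference 15 points, SD 17.2, two-sided alpha 5%.

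**Inputs assumed, because the protocol gives none.** True 24-month failure risk R of 10%, 20% or 30%; constant rates of failure and withdrawal; withdrawal independent of failure; and, where shown, a split of dropout by arm.

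**The plan's own figure first.** 75 × 0.80 = 60 evaluable, 30 per arm. 15 / (17.2 × √(2/30)) = 15 / 4.441 = 3.378, and Φ(3.378 − 1.960) = Φ(1.418) = 92.2%. A noncentral t calculation gives 91.3% (57 df), or 91.2% (49 df, centres fitted). The stated power of over 90% reproduces, and nothing below alters it.

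**Formulas for failures.** With dropout D, let f = −ln(1 − R) and w = −ln(1 − D) be the cumulative hazards over 24 months.
- Share of all randomised patients: A = f/(f + w) × [1 − exp(−(f + w))]
- Share of known status: K = A / [A + (1 − R)(1 − D)]

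Example, R = D = 20%: f = w = 0.223 and exp(−0.446) = 0.64. So A = 0.5 × 0.36 = 18.0%, and K = 0.18 / (0.18 + 0.64) = 22.0%.

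**At the planned 20% dropout:**

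| True risk | All randomised | Known status |
|---|---|---|
| 10% | 9.0% | 11.1% |
| 20% | 18.0% | 22.0% |
| 30% | 27.1% | 32.6% |

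The error is 1.0 to 2.9 points downwards or 1.1 to 2.6 points upwards. If every failure came after the dropouts, the all-randomised figure would be R × 0.80, that is 8%, 16% and 24%, an error of 2 to 6 points.

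**Between arms, equal dropout of 20%.** True 30% against 15% (difference 15 points) reads as 27.1% − 13.5% = 13.6 points of all randomised, or 32.6% − 16.5% = 16.0 points of known status (differences taken before rounding).

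**Between arms, unequal dropout.** Suppose the 15 dropouts fall 12 against 3: 12/37.5 = 32% and 3/37.5 = 8%.

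| True risk | All randomised | Known status |
|---|---|---|
| 20% vs 20% | 16.7% vs 19.2% | 23.5% vs 20.7% |
| 22% vs 20% | 18.4% vs 19.2% | 25.8% vs 20.7% |

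In the first row the arm with more withdrawals looks 2.5 points better with one denominator and 2.8 points worse with the other. In the second row the all-randomised figure reverses the true order.

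A harsher split, dropout 30% against 10% with true risks 30% against 15%, gives 25.5% vs 14.3% (difference 11.2) or 34.2% vs 15.7% (difference 18.5), against a true difference of 15.

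**The case against.** The strongest reply is that this is a descriptive secondary outcome with no planned test, that the failure risks are invented, and that the distortion lies well inside sampling error. With 37.5 per arm and risks of 30% and 15%, the 95% half-width for the difference is 1.96 × √(0.30 × 0.70/37.5 + 0.15 × 0.85/37.5) = 18.6 points. An error of 1 to 3 points is small beside that. This stands, and it limits the weight of the point. It does not defend reporting no interval at all.

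A second reply is that an article commonly leaves the denominator to the analysis plan. That is fair, and an unstated denominator alone would be no finding. What the article does fix is the method, and that method contains neither a comparison nor an allowance for incomplete follow-up.

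A reader might go further in three ways that the document does not support.
- *The arm with more withdrawals will look better.* This holds only if all randomised patients form the denominator; with known status that arm looks worse.
- *No simple percentage can be right.* If withdrawal is unrelated to failure, the failure share among patients followed to 24 months is unbiased.
- *Failure is the secondary outcome freest of self-report.* One route to failure uses KOOS, the surgical route is a choice made by unblinded patients and clinicians, and the MRI and X-ray scores use no questionnaire.

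The plan also has partial safeguards: withdrawal reasons go on a dropout form, and intercurrent events are to be listed by arm.

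**Conclusion.** The point holds in a limited form. The stated analysis gives no between-arm estimate or interval for an outcome that the abstract says will be compared, and it ignores that follow-up ends at withdrawal. At the planned dropout the error is about 1 to 3 points per arm for true risks of 10% to 30%, and up to 6 points if failures come late. These sizes rest on assumed risks and independent withdrawal, and the per-arm 1 to 3 points also on constant rates. Withdrawal related to failure could make them larger. The direction between arms cannot be stated until the denominator is known. Sample size and primary analysis are untouched. A better method is available at little cost, so the change is worth making, but nothing here undermines the trial's main conclusion.

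**What to change.** Keep the frequencies and percentages as description, and state their denominator. Then add:

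- The cumulative incidence of first failure by 24 months, in all randomised patients, by arm. Surgery-based failures count at the reported date and KOOS-based failures at the visit where they are found. Withdrawals are censored at last contact, and death is a competing event. Report the between-arm difference with its 95% CI.
- A list of withdrawals before failure, by arm and reason.
- A sensitivity analysis that treats withdrawals after treatment as failures. Show separately the patients never treated because manufacture failed or the product was contaminated. Counting them as failures would penalise the N-TEC arm alone for something that is not treatment failure.

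The cost is analysis wording and a few lines of code; visits, eligibility and sample size do not change. The sponsor should confirm that dates of later surgery are captured, because the protocol does not say so expressly. The limits should be stated with the result: intervals will be wide with few events, KOOS-based failures are dated only to a visit, and censoring assumes that withdrawal is unrelated to failure, which is what the sensitivity analysis tests.

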### Interim analyses {21b}

No interim analysis is planned.

### Methods for additional analyses (eg, subgroup analyses) {20b}

No subgroup analysis is planned.

### Methods in analysis to handle protocol non-adherence and any statistical methods to handle missing data {20c}

Multiple efforts will be undertaken to retrieve missing data. No missing values are anticipated in the baseline characteristics. For the primary endpoint, the pattern of missing data will be systematically assessed. In the event of death, missing data will be assumed to be completely at random and will not be imputed. In cases of loss to follow-up, data will be assumed to be missing at random, and multiple imputations using chained equations will be considered.

### Plans to give access to the full protocol, participant level data and statistical code {31c}

Information on the study will be disseminated through websites of the hospitals or newsletters designed with the patient board of the study. The publication of the results is planned through submission of papers to peer-reviewed journals. In addition, the results will be communicated at national and international conferences and seminars as well as through presentations for lay persons. Study results will be published in the registered databases.

## Oversight and monitoring

### Composition of the coordinating centre and trial steering committee {5d}

It is a multicentre study with the University Hospital Basel as the leading centre. The following persons and committees are involved:

The sponsor-investigator also acts as the principal investigator and is responsible for coordinating the clinical trial across participating partners, ensuring harmonisation of procedures in addition to fulfilling all other sponsor and investigator duties. The Sponsor’s institution will also provide regulatory oversight and support for the trial submission and conduct. The principal investigators are responsible for the conduct of the clinical trial in accordance with GCP regulations and ICH-guideline E6 (R2). They are involved in the design and planning of the clinical trial and are responsible for all trial-related medical decisions at their site. Furthermore, they have the responsibility of training all further staff involved in the performance of the clinical trial at their site and reporting of all serious adverse events (SAEs) to the Sponsor-Investigator. The steering committee, consisting of the patient board and principal investigators, will convene one to two times per year, depending on the needs and phase of the study’s development. The patient advisory board consists of two patient representatives of patient organisations related to OA field and one patient previously treated with N-TEC.

The power analysis for the study has been conducted by the Department of Clinical Research at the University Hospital Basel. Serological tests will be carried out by the laboratories at the designated hospitals across the clinical sites. Monitoring will be performed by the Department of Clinical Research of the University Hospital Basel for all clinical sites, except Croatia, where monitoring will be carried out by Smart Medico d.o.o in coordination with the Department of Clinical Research at of the University Hospital Basel. The graft will be manufactured in GMP-compliant facilities in Germany at the University Hospital Würzburg and Switzerland at the University Hospital Basel, with a manufacturing authorisation from Government of Upper Franconia, Ansbach, Germany in consultation with the Paul-Ehrlich-Institute (NCA) or Swissmedic, Switzerland, depending on the manufacturing site.

### Composition of the data monitoring committee, its role and reporting structure {21a}

The monitoring will be performed by the Department of Clinical Research of the University Hospital Basel for all centres, except Croatia. A monitoring plan, describing in detail the documents and data to be monitored, has been established to guarantee a harmonised monitoring. An initiation visit is carried out before the start of the trial, interim visits and a close-out visit at the end of the trial are foreseen for each site. All source data and documents will be accessible to monitors and questions arising from monitoring will be answered by the participants of the audit from the site.

### Adverse event reporting and harms {22}

During the entire duration of the study (category C), all adverse events (AE) and all SAEs are collected, fully investigated and documented in source documents (patient’s records) and CRFs. Study duration encompasses the time from when the participant signs the informed consent until the last protocol-specific procedure has been completed and includes a safety follow-up period of up to 2 years.

### Frequency and plans for auditing trial conduct {23}

The responsible ethics committees, authorities and the sponsor have the right to and may inspect the study and/or manufacturing site at any time prior to, during or after the clinical conduct. There will be no audits in addition to the monitoring and inspections. Study documentation and the source data/documents are accessible to auditors/inspectors (also CEC and CA) and questions will be answered during inspections. All involved parties must keep the participant data strictly confidential.

### Plans for communicating important protocol amendments to relevant parties (eg, trial participants, ethical committees) {25}

In case of important protocol modifications (eg, changes to eligibility criteria, outcomes, analyses), relevant parties (eg, investigators, CEC, competent authorities, trial registries, regulators) will be notified within 5 days. Under emergency circumstances, deviations from the protocol to protect the rights, safety and well-being of human subjects may proceed without prior approval of the sponsor and the CEC/CA. Such deviations shall be documented and reported to the sponsor and the CEC/CA as soon as possible.

### Dissemination plans {31a}

The study was registered in an online trial registry clinicaltrials.gov. Information on the study will be disseminated through websites of the hospitals or newsletters designed with the patient board of the study. The study protocol will be published as an open access version. The publication of the results is planned through submission of papers to peer-reviewed journals. In addition, the results will be communicated at national and international conferences and seminars as well as through presentations for lay persons. Study results will be published in the registered databases, if applicable.

## Discussion

The aim of this study is to evaluate the use of N-TEC in comparison with PRP as a standard treatment option for patients with isolated PFOA. Safety, pain, function and structural outcomes of both treatments are compared. In addition, the study is complemented with a health-economic evaluation to establish the intervention’s value for money and impact on productivity in working age individuals.

Currently, no regenerative treatment options exist for PFOA. This study is the first RCT to evaluate the efficacy of N-TEC and the first to investigate a regenerative intervention in this condition. A previous study demonstrated promising results for N-TEC in the treatment of focal chondral lesions of the knee joint.^42^ Furthermore, its safety and feasibility were confirmed in case studies with OA^43^ as well as pilot patients treated under temporary authorisation in Switzerland suffering from PFOA (unpublished results).

A notable strength of this study is the combination of both subjective and objective outcome measures. In addition to PROMs, the study design includes objective criteria such as radiographic and MRI assessments, activity monitoring and standardised physiotherapeutic evaluations. Although postoperative physiotherapy is delivered at various locations, all participating physiotherapists receive individualised training in the standardised rehabilitation protocol. This ensures a uniform application of core treatment principles, while still allowing for patient-specific adaptations.

Nevertheless, the study has certain limitations. Due to the inclusion of a non-surgical comparator, blinding of participants is not possible, which may introduce bias. Also, a surgical approach may be seen by some patients as potentially having greater benefit, which may also introduce bias in the patient self-reported outcome.

### Trial status

Recruitment started on 6 June 2024. The planned duration of recruitment after the start is 2 years, and the last follow-up measurement takes place 2 years after the last intervention.

### Availability of data and materials {29}

The complete dataset is then exported and transferred to the study statistician as well as the principal investigator through a secure channel. A suitable subdataset is transferred to the study health economist, following the same principles as for the statistical analysis. The exported data will be archived for 10 years by the principal investigators in the respective centres.

### Ethics and dissemination

All centres involved in the implementation of the intervention have obtained approval from their respective competent ethics committees. This includes approval from the following ethics committees: Ethics Committees of North-Western and Central Switzerland (EKNZ): 2024–00075 (associated ethical committees: Cantonal Ethics Committee Bern, Cantonal Research Ethics Commission Geneva (CCER), Cantonal Ethics Committee Ticino, Cantonal Ethics Committee Zurich). The EKNZ covers several cantons in Switzerland, including Basel. The site in Lugano falls under the Cantonal Ethics Committee, Ticino. Ethics Germany, according to CTIS: 2023-508640-21-00 (Medicinal Ethical Commission of the Julius-Maximilians-University Wuerzburg, Ethical Commission of the Albert-Ludwigs-University Freiburg) and Central Ethical Committee Croatia, Republic of Croatia Ministry of Health: 2023-508640-21-00. The Swissmedic reference number is 701788.

Participation in the study is voluntary, and all participants are required to provide written informed consent. Participants may withdraw their consent at any time without providing a reason and without any negative consequences. Data will be collected only from patients who have given their written consent to our study. Their medical records will be handled confidentially. Only members of the study team, monitors and the respective authorities (ethical committees, competent authorities) will have access to the data.

The study was registered in an online trial registry clinicaltrials.gov. Information on the study will be disseminated through websites of the hospitals or newsletters designed with the patient board of the study. The study protocol will be published as an open access version. The publication of the results is planned through submission of papers to peer-reviewed journals. In addition, the results will be communicated at national and international conferences and seminars as well as through presentations for lay persons. Study results will be published in the registered databases, if applicable.
